### 3.4 Study Selection Criteria

The study selection criteria are outlined below:

#### Inclusion criteria

1. At least two consecutive eGFR laboratory tests with values  $\geq 30$  and  $< 60$  mL/min/1.73 m^2 (Stage 3A or 3B) that are  $> 90$  and  $\leq 730$  days apart. The index date is the date of the second eGFR measure meeting the criteria for stage 3 CKD
2. At least 12 months of continuous presence in the database or registration in the data prior to the first qualifying eGFR (for data sources with information on enrollment)
3. Age  $\geq 18$  years at index date

#### Exclusion criteria

Patients will be excluded if they meet the following criteria:

1. Solid organ transplant before the study index date
2. Any evidence of advanced CKD (stage 4, 5) based on CKD diagnostic codes, or renal replacement therapy before the index date

### **3.5 Participant Follow-up**

CKD diagnosis status will be assessed using data from the  $\geq 12$ -month baseline period until six months post-index for the calculation of undiagnosed CKD prevalence. To assess time to CKD diagnosis (primary objective 2), patients will be followed from the index date to the earliest of their follow-up end date (due to death or transfer out of database) or end of data coverage period

To assess CKD management and monitoring quality indicators (secondary objective 3), patients will be followed starting from the six months post index date until the follow-up end date (due to death or transfer out of the database) or end of data coverage, whichever comes first.

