### CRDS Database (China)

In December 2018, the National Clinical Research Center for Kidney Disease, the Center for Chronic Non-communicable Disease Prevention and Chinese Center for Disease Control and Prevention jointly established the Chinese Renal Disease Data System (CRDS). By the end of

November 2022, the CRDS database contained 24 Grade 3A hospitals, including 16,953,679 patients with data collected from 1994 to 2022, and consisting mostly of hospital-wide data. Data governance has been completed in 19 hospitals with 15,245,055 patients. The data of rest 5 hospitals has been governed in the CRDS database after 2022 and given the characteristics and of the CRDS database, we will exclude hospitals with data only from nephrology departments; with 20 remaining hospitals that will be included. Observation start date will be January 1 2015 and observation end date will be 31 December 2020 according to quality and situation of CRDS database.

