### 3.3 Study Population

Patients  $\geq 18$  years old with two consecutive eGFR measurements indicating stage 3 CKD ( $\geq 30$  and  $< 60$  mL/min/1.73m^2 using CKD-EPI (preferred) or MDRD equation) recorded more than 90 days apart (max. 730 days), meeting the inclusion criteria will be included in the study and constitute the denominator for the calculation of the prevalence of undiagnosed stage 3 CKD. A subset of the study population will be identified with no encounters with a diagnosis code for CKD any time prior to the study index date (for primary objective 2). The observation period will vary based on the period of data coverage, which may be unique to each data source. In CRDS database observation start date will be January 1, 2015, and observation end date will be 31 December 2020.

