### **4.2 Outcomes**

#### **Case Definition – Undiagnosed Stage 3 CKD**

Patients with undiagnosed stage 3A-3B CKD will be identified if they have no healthcare encounter with a diagnosis code for CKD at any time during the  $\geq 12$ -month lookback period before the first eGFR measurement and up to 6 months post-index date (baseline period). Those with a documented diagnosis of CKD during this time period will be considered as having diagnosed CKD. It will be assumed that patients with at least one diagnostic code for CKD during the above specified time window have diagnosed CKD. 错误!未找到引用源。 below shows the study schematic.

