## **5. STATISTICAL ANALYSIS PLAN**

### **5.1 Statistical Methods – General Aspects**

This study is purely descriptive without any formal hypotheses. The main focus will be on quantifying the prevalence and consequences of undiagnosed CKD. Key assumptions include: our ability to define undiagnosed CKD subjects with only eGFR as an indicator of a future diagnosis of CKD by a physician, secondly, that absence of claims or health record data for CKD or other comorbid events indicate that the diagnosis of the condition never occurred, and finally, the timing of recorded CKD diagnosis in the database corresponds with the time when the first CKD diagnosis was made by the health care provider (assuming minimum lag in data recording).

Missing data for baseline measures will be assessed and addressed as a categorical variable with a level for missingness. All reported measures will be summarized in the study tables. Point estimates and their 95% C.I.s will be presented in the final analyses.

Data analysis will take place in a step-wise approach where the objectives pertinent to the describing the undiagnosed CKD patient cohort will be performed first and results will be reviewed by the study team before the analysis on the rest of the objectives take place.

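### The 6-month diagnosis window runs past the stated end of observation for patients indexed after 30 June 2020, which biases undiagnosed prevalence upward, mainly in the 2020 trend point

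*Protocol*

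**What the plan says.** - **Window.** Section 3.5 assesses diagnosis status from the "baseline period until six months post-index for the calculation of undiagnosed CKD prevalence". The case definition in section 4.2 uses the same end point. It has two categories only, diagnosed and undiagnosed, and none for a window that was not fully observed.
- **Missing codes.** Section 5.1 assumes that "absence of claims or health record data for CKD or other comorbid events indicate that the diagnosis of the condition never occurred".
- **Index date.** Section 3.4: "The index date is the date of the second eGFR measure meeting the criteria for stage 3 CKD". No latest permitted date is given.
- **Observation time.** Section 3.4 asks for "At least 12 months of continuous presence in the database or registration in the data prior to the first qualifying eGFR" (for sources with enrolment information). Neither the inclusion nor the exclusion criteria require any time after index.
- **End of observation.** The CRDS description in section 3.2 says the "observation end date will be 31 December 2020 according to quality and situation of CRDS database". It also says that the database has "data collected from 1994 to 2022".
- **Denominator.** Section 5.2 uses all individuals who meet the inclusion criteria (cohort 1).
- **Trend rule.** Under section 5.2, Trends over time, a patient whose first code comes less than 6 months after the qualifying eGFR counts as diagnosed in the index year, even if the code falls in the next calendar year.

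**The concern.** Followed as written, these provisions cannot all be met for late-2020 patients. Someone indexed on 1 December 2020 has one month of observation, not six. A code entered in March 2021 should make that patient diagnosed under both the case definition and the trend rule, but it lies after the stated end of observation. The patient is then counted as undiagnosed.

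Shortening the window can only move patients from diagnosed to undiagnosed, so the direction of the bias is known, and a larger sample does not reduce it. It falls mainly on the last point of the calendar-year series (secondary objective 1), where it could create a rise or hide a fall. The same patients sit in the undiagnosed group of the baseline comparison and the logistic model.

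The protocol deals with incomplete follow-up elsewhere: time to diagnosis is censored, and the quality indicators are also reported in a complete-follow-up subset. The primary prevalence has neither.

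**Working it through.** **The plan's own figure.** Section 5.5 gives 1,000 patients for ±3 points at a prevalence of 60% to 80%. With n = 1.96² × p(1−p) / 0.03², the requirement is 1,025 at 60%, 897 at 70% and 683 at 80%. At n = 1,000 the margins are ±3.04, ±2.84 and ±2.48 points. The stated figure is reproduced, and the sample size is not at issue.

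**Half-widths for comparison.** From 1.96 × √(p(1−p)/n):
- n = 27,000 (section 5.5): 0.58 points at 60%, 0.48 at 80%.
- One calendar year, assuming an even spread, 27,000 / 6 = 4,500: 1.43 points at 60%, 1.17 at 80%.

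**Share of patients with a shortened window.** Assume index dates uniform in time and a 183-day window.
- 2020: 183 / 366 = 50%.
- All index dates from 1 January 2015: 183 / 2,192 = 8.4%.
- All index dates from 1 April 2016 (if the 12-month lookback and the gap of more than 90 days must fall inside the observation period): 183 / 1,736 = 10.5%.

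**Share of the 6-month codes that is lost.** Let g be the share of the cohort whose first CKD code falls within 6 months after index. The protocol does not give g, so it is assumed. The bias in points is 100 × g × L, where L is the fraction of those codes cut off. With r days left before the cut-off, the fraction captured is r/183 for even coding, or (1 − 2^(−r/h)) / (1 − 2^(−183/h)) for coding that clusters early with half-life h days. L is 1 minus the average of this fraction over index dates.

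| Coding pattern | L, 2020 | L, from 2015 | L, from April 2016 |
|---|---|---|---|
| Even over 6 months | 0.251 | 0.042 | 0.053 |
| Half-life 60 days | 0.169 | 0.028 | 0.036 |
| Half-life 30 days | 0.112 | 0.019 | 0.024 |
| Half-life 14 days | 0.057 | 0.009 | 0.012 |

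**Upward bias in points for g = 5%, 10%, 20%.**
- 2020, even coding: 1.3, 2.5, 5.0. Half-life 14 days: 0.3, 0.6, 1.1.
- Overall from 2015, even coding: 0.2, 0.4, 0.8. Half-life 14 days: 0.05, 0.1, 0.2.

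**Upper end.** If 20% are coded by index and 30% of the rest are coded evenly over 6 months, g = 0.8 × 0.3 = 24%. The bias is 24 × 0.25 = 6.0 points for 2020 and 24 × 0.053 = 1.3 points overall (index dates from April 2016).

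**An example inside the planning range.** If 20% are coded by index and 20% of the rest are coded evenly over 6 months, the true prevalence is 0.8 × 0.8 = 64.0%. Patients indexed in July to December 2020 have half a window on average and show 0.8 × 0.9 = 72.0%. The year 2020 then shows (64.0 + 72.0) / 2 = 68.0%, an excess of 4.0 points. The overall excess is 8.0 × 0.084 = 0.7 points, or 8.0 × 0.105 = 0.8 points with index dates from April 2016.

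**The case against.** **The end of observation may not be the end of the data.** CRDS holds data to 2022. The Synopsis places the qualifying eGFR values within the observation period, which could make that period an accrual window, and section 3.5 ends follow-up at the end of data coverage, a different term. The trend rule makes no exception for 2020. If codes from early 2021 are read, the calendar cut-off disappears. This stands as a possible reading, but no sentence says that 2021 codes will be used. Section 3.3 ties the observation period to data coverage, and the 2020 end was chosen because of the quality and situation of the database. The Figure 1 schematic is not shown and may carry a cut-off; the text has none.

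**Three stronger claims that a reader might infer, and that the protocol does not support.**
- *Every patient indexed after June 2020 is undiagnosed by default.* Patients coded before index, or between index and year-end, remain diagnosed. In the example above that is 28% of the late-2020 patients.
- *Early deaths add to the bias.* A patient who dies without a code was never diagnosed in the data and meets the case definition.
- *The primary estimate should be limited to patients observable for 6 months.* That conditions on survival and retention after index. No enrolment data are described for CRDS, so observability might have to be inferred from later visits, which would select frequent attenders.

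**The size may be small.** With codes clustered soon after index the bias is 0.3 to 1.1 points for 2020 and 0.05 to 0.2 overall. The 6-point maximum implies a true prevalence of 0.8 × 0.7 = 56%, below the 60% to 80% planning range. The overall bias stays below the planned ±3 points in every scenario. All of this stands.

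**Conclusion.** The point holds as an unresolved conflict between the 6-month window and the stated end of observation. Unless codes after 31 December 2020 are read, patients whose first code falls after that date but within 6 months of index are misclassified as undiagnosed, and prevalence is biased upward.

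Under the assumptions above (uniform index dates, g from 5% to 24%, coding from even to a 14-day half-life), the bias is roughly 0.3 to 6 points for 2020 and 0.05 to 1.3 points overall. The 2020 figure can exceed that year's sampling error of about 1.2 to 1.4 points. The overall figure ranges from negligible to about twice the half-width of 0.5 to 0.6 points. Only the direction is certain; the size rests on coding rates and timing that the protocol does not give. The 2020 trend point is the result most exposed.

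**What to change.** State one of the following in sections 3.3 to 3.5 before the data are extracted:
1. The last permitted index date is 30 June 2020, and July to December 2020 is used only to look for codes.
2. All 2020 index dates are kept, and CKD codes are read to 30 June 2021, provided the post-2020 CRDS data are judged of adequate quality.

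Either change removes the calendar cut-off. As a sensitivity analysis, not as the primary estimate, report prevalence among patients with 6 months observable (coded and uncoded alike), or the proportion uncoded at index multiplied by the Kaplan-Meier proportion still uncoded at 6 months.

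**Cost.** Option 1 loses about 8 to 10% of index patients, leaving 27,000 × 0.895 ≈ 24,200 to 27,000 × 0.916 ≈ 24,700. At about 24,000 and 60% prevalence the half-width is 1.96 × √(0.24/24,000) = 0.62 points instead of 0.58. The 2020 trend point would then cover half a year and should be labelled so. Option 2 needs a longer code extract and a check of its quality.

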### Sensitivity Analysis

To calculate the robustness of our undiagnosed CKD definition (identified through 2 eGFR measures and no ICD-9/10 CKD diagnosis codes, and OHDSI ICD-10 CN2016 is used in the CRDS database), we will conduct sensitivity analyses 1-2 that assess whether the lack of healthcare encounters, as originally defined, truly captures an undiagnosed population.

Sensitivity analysis for undiagnosed CKD includes ICD-9/10 diagnosis codes for stage 3 CKD or higher

Sensitivity analysis for undiagnosed CKD includes ICD-9/10 diagnosis codes for CKD based on a broader definition derived by Winkelmayr *et al.*, 2005 ([section 8](#)). We will conduct sensitivity analysis 3 to assess if we have included sufficient individuals with undiagnosed CKD in the database, as required by study inclusion [criteria 2](#).

Sensitivity analysis for adjustment of inclusion criteria 2 from “at least 12 months of continuous presence in the database or registration in the data prior to the first qualifying eGFR (for data sources with information on enrollment)” to “at least one medical visit with diagnostic record within  $\leq 12$  months prior to the first qualifying eGFR”. There are no changes in any other inclusion and exclusion criteria. Analyze undiagnosed CKD according to the primary study definitions using eGFR measures captured within a specific time period prior to diagnosis.

- *Time to CKD diagnosis*

For the cohort of patients with no CKD diagnosis code as of the study index date (cohort 2), the median (95% CI) time in days/months from the study index date to physician-diagnosed CKD (using the primary CKD study definition) will be calculated using the Kaplan-Meier method. Survival times will be censored as of the last day of follow-up for patients who remain undiagnosed by a physician. Time to physician diagnosis of CKD will be calculated overall and by patient characteristics and comorbidities. If possible, association between baseline characteristics and time to CKD diagnosis will be assessed using relevant regression models. The time to physician diagnosed stage 3 CKD or higher (sensitivity analysis #1) and the time to CKD using a broader definition (sensitivity analysis #2) ([section 8](#)) will also be calculated.

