### **5.3.3 Study Limitations**

Although large retrospective databases can be used to identify and track cohorts of patients representing real-world populations, the results of this study should be considered in the context of the biases that are inherent to this type of design.

This study is subject to the following limitations:

- Data collected in a real-world setting may lack information on specific covariates and laboratory investigations. We will, however, assess the level of covariate missingness. The potential impact of missingness on the outcome of interest will be investigated.
- Coding may be a limitation itself due to sensitivity and specificity, and caution is required when interpreting any clinical associations.
- The analysis will examine the proportion of undiagnosed CKD among those who are tested/screened for CKD only; this could have the effect of biasing the proportion of undiagnosed versus screening all individuals for CKD.
- There is a risk of misclassification (diagnosed vs. undiagnosed) if CKD diagnosis is made in clinical settings that do not contribute data to the selected database.
- The generalizability of the results of this study may not be applicable to CKD patients who differ from the study population or countries not included in the analysis.
- There may be unmeasured confounding that may have an impact on risk estimates and may differ between countries and settings

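### The end-of-follow-up rule for time to CKD diagnosis has no provision for patients who silently stop attending CRDS hospitals, so unless CRDS captures transfer out they stay at risk to the end of 2020

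*Protocol*

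**What the plan says.** Section 3.5 sets the follow-up for time to diagnosis, which runs from index to the earlier of "follow-up end date (due to death or transfer out of database) or end of data coverage period". Section 5.2 (Time to CKD diagnosis) takes the censoring date from this: "Survival times will be censored as of the last day of follow-up for patients who remain undiagnosed by a physician". The median and its interval "will be calculated using the Kaplan-Meier method" in cohort 2, the patients with no CKD code as of index.

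Section 3.2 describes the source. By November 2022 "the CRDS database contained 24 Grade 3A hospitals", "consisting mostly of hospital-wide data", and 20 of these hospitals will be used. "Observation start date will be January 1 2015 and observation end date will be 31 December 2020". No registered or insured population is described, and the protocol does not say how leaving the database would be recognised.

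Three other places bear on the point. Section 5.1 lists as a key assumption that a missing record means the diagnosis did not occur. Section 5.3.3 concedes a risk of misclassification "if CKD diagnosis is made in clinical settings that do not contribute data to the selected database". Inclusion criterion 2 asks for 12 months of presence before the first qualifying eGFR, with a qualifier limiting it to sources that hold enrolment information. Nothing comparable is required after index.

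**The concern.** Ending follow-up at death, transfer out or end of data works where membership is recorded, as in an insurer or a registered practice list, because leaving produces a date. In hospital records a patient who moves to another provider usually just stops appearing. If CRDS holds no transfer date, the rule as written keeps that patient in the Kaplan-Meier denominator to the end of 2020, and section 5.1 counts the silence as continued absence of diagnosis. The curve then mixes patients not yet diagnosed with patients who can no longer be observed.

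Median time to diagnosis is the outcome of primary objective 2. It could be lengthened, or not reached at all, for reasons unrelated to diagnostic practice. Objective 1 has a related weakness: a patient with no earlier code and no contact in the six months after index is classed as undiagnosed.

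No planned analysis tests this. Sensitivity analyses 1 and 2 change the code list, and sensitivity analysis 3 changes the look-back criterion. The complete-follow-up subset in section 5.2 applies to the quality indicators only, and only where enrolment data exist.

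**Working it through.** **The plan's own figure.** The protocol gives no precision or expected value for time to diagnosis. Its only precision figure is ±3 points for prevalence with 1,000 patients (section 5.5). The half-width 1.96·√(p(1−p)/1000) is 3.04 points at 60% and 2.48 at 80%. The figure reproduces, but it does not bear on this point.

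**Inputs from the protocol.** The window runs from 1 January 2015 to 31 December 2020, which is 2,191 days. The two eGFRs must be more than 90 days apart, so the longest possible follow-up after index is about 2,191 − 91 = 2,100 days (69 months). If the 12-month look-back must also fall inside the window, it is 1,735 days (57 months).

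**Assumed inputs, not in the documents.** True median m of 12, 24 or 36 months with exponential time to diagnosis; loss independent of diagnosis; end of data independent of both. A diagnosis after loss is not seen, and the patient stays at risk to the end of data.

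**Model A, all loss at index.** A share f never returns. The curve estimated under the planned rule is S(t) = f + (1−f)·2^(−t/m). Setting S = 0.5 gives t = m·log2[(1−f)/(0.5−f)]. For m = 24 and f = 0.2, 24·log2(0.8/0.3) = 34.0 months.

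**Model B, gradual loss.** Diagnosis rate λ = ln2/m per month; loss rate μ = −ln(1−L)/12 for a yearly loss L. The diagnoses seen by time t accumulate as F(t) = [λ/(λ+μ)]·(1−e^(−(λ+μ)t)). For m = 24 and L = 0.2, λ = 0.0289 and μ = 0.0186, so the ceiling λ/(λ+μ) is 0.608 and F reaches 0.5 at 36.3 months. For L = 0.4, μ = 0.0426 and the ceiling is 0.404, so the median is never reached. A simulation with 200,000 patients per scenario and follow-up uniform over 0 to 69 months gave 28.0 months, 36.3 months and not reached at 10%, 20% and 40% per year, in line with the formula.

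Median in months under the planned rule (Model B from the formula):

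| True median | Loss | A: at index | B: per year |
|---|---|---|---|
| 12 | 10% | 14.0 | 12.9 |
| 12 | 20% | 17.0 | 14.2 |
| 12 | 40% | 31.0 | 20.2 |
| 24 | 10% | 28.1 | 28.0 |
| 24 | 20% | 34.0 | 36.3 |
| 24 | 40% | 62.0 | not reached |

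With a true median of 36 months, Model B gives about 46 months at 10% per year and no median within 69 months at 20%. If follow-up is limited to 57 months, the 62-month entry would also not be reached. In the simulation, censoring at the moment of loss returned the true median to within 0.3 months in every scenario, and with no loss the two rules agreed.

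**Check on the remedy.** Censoring at the last encounter with no added window was simulated with nobody leaving, a 24-month median to the point at which a diagnosis becomes due, and diagnoses recorded only at visits. With a mean visit gap of 6 months the median was 27.9 against a true 30.5. With a gap of 12 months it was 30.7 against 37.1. Censoring at the end of data gave 30.8 and 37.0. Last-contact censoring therefore errs short when patients have not left.

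**The case against.** Four arguments weigh against the point.

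*CRDS may capture transfer out.* The protocol does not say that it lacks such data. The feasibility counts are about 27,000 under the main criteria and about 46,000 under sensitivity analysis 3, which changes only criterion 2. At least 19,000 of 46,000 (41%) therefore fail the presence criterion, so it is being applied and some working definition of presence exists before index. This stands, and it is why the point is conditional. The same counts show that continuous presence cannot be assumed in this source, although they do not measure loss after index.

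*The definition belongs in the SAP.* A SAP could define transfer out by inactivity without contradicting section 3.5. That is true of the definition. But the protocol itself fixes the events that end follow-up, and followed literally they leave silent leavers at risk.

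*The weakness is disclosed.* Sections 5.1, 5.3.1 and 5.3.3 acknowledge misclassification of status. None connects it to follow-up time, and no analysis of objective 2 follows from it.

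*The direction is not certain.* A reader might infer that the reported median will simply be too long. The documents do not support that. A patient diagnosed elsewhere before index enters cohort 2 as having no code, and the first CRDS code then looks like a quick new diagnosis, which shortens the median. Only the effect of silent departure taken alone has a known sign. The entry rule (two eGFRs more than 90 days apart, with earlier presence) also favours repeat attenders, so loss may be at the low end of the assumed range.

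**Conclusion.** The point holds conditionally. If transfer out is not captured in CRDS, the rule in sections 3.5 and 5.2 keeps unobservable patients at risk, and nothing planned shows how much this affects primary objective 2. For an assumed true median of 24 months the shift is about 4 months at 10% loss and 10 to 12 months at 20%. At 40% the median becomes 62 months or is not reached. These figures rest on assumed loss, an exponential time to diagnosis and independence of loss from diagnosis. The documents give neither the loss rate nor the true median, so both the size and the net direction remain open.

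Two further readings go too far. The planned curve and a last-contact curve are not strict bounds: if leavers are diagnosed elsewhere sooner than stayers, the truth lies below both. Nor can it be said that prevalence in objective 1 is overstated by a given amount. Patients without a contact in the six-month window can raise it, but no size has been derived. The point warrants a change because that change is cheap and protects a primary objective.

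**What to change.** 1. State how transfer out of the database is determined in CRDS. If it is already captured, or already means a period of inactivity, one sentence saying so largely settles the point.
2. Prespecify a sensitivity analysis of primary objective 2 that censors undiagnosed patients at the last recorded encounter of any kind plus a fixed inactivity window, for example 12 months, and no later than death or end of data. Show it beside the planned curve as a robustness range, not as bounds.
3. For objective 1, report as supportive only the share of patients with any encounter in the six months after index and the prevalence of undiagnosed CKD among them. State that this conditions on later attendance and so describes a different population.

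The cost is one additional censoring date, one curve and one table from data already held. The downside is that last-contact censoring shortens follow-up, is itself informative and can bias the median short, so it should accompany the planned analysis and not replace it.
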